### Study population

To assess feasibility, acceptability, and impact of the model, different stakeholder groups will form our study population. Each outcome will require a different sampling frame as described below.

#### Feasibility of implementing the PrIMO model using the SIC

Primary care clinics participating in this study will serve as the unit of observation for the primary outcome and will be tracked as they move through site-specific activities related to planning for model implementation, model launch, and achieving competency with PrIMO as the standard model of care for OUD.

#### Acceptability of the PrIMO model

Adult, English-speaking, individuals who are not incarcerated and who are willing to provide consent will contribute data in two distinct convenience sample groups: site staff and patients receiving MOUD treatment. Among the site staff, a range of site staff participants employed by the primary care clinic or pharmacy in one of four roles will be eligible: provider (5–20 per site; may include MD, DO, NP, PA, nurse, behavioral health providers, and/or other clinical roles that provide care to patients), pharmacist (2–6 per site), pharmacy technician (2–10 per site), or administrator (2–10 per site; may include CEO, CFO, CMO, clinic managers, front desk staff, and/or other administrative roles that oversee programming at the clinic). A subset of site staff participants (up to 11 per site) also will be invited to participate in qualitative interviews. Site staff participants will be recruited for qualitative and quantitative measurements. Patient participants (12–40 per site) will also be English-speaking, not prisoners, willing and able to provide consent, and be receiving MOUD from the participating clinic and exposed to the model for at least 14 days to be eligible for the study. A subset of patient participants (up to 12) will be invited to participate in qualitative interviews. Patient participants will be recruited on an ongoing basis for a period of 6 months post-PrIMO launch.

#### Impact of the PrIMO model

EHR data from each site will be extracted throughout the study period for all adult patients receiving MOUD. Extracted EHR data will span 1 year pre-model launch and 1-year post-model launch to explore impact at each clinic.

### Processes and measures

#### Feasibility

Feasibility of launching the PrIMO model will be assessed using the SIC. The SIC is an eight-stage tool that tracks implementation processes and milestones, with stages spanning three implementation phases: pre-implementation (stages 1–3), implementation (stages 4–7), and competency (stage 8) [41–49]. The SIC is a date-driven measure with item responses including the date by which implementation activities are completed. The SIC yields three scores: (1) Duration—time to complete implementation activities, (2) Proportion—percent of activities completed, and (3) Final stage—the furthest point in the implementation process achieved. The SIC also gathers project-specific, site-level characteristics identified a priori that may impact implementation. This tool has been adapted for many evidence-based practices including mental health, school prevention programs, primary care interventions, substance use disorder treatments, and large state system initiatives; a “universal” tool has been developed for use of monitoring of general implementation strategies [50]. Results from studies using the SIC have repeatedly shown that when there is variability among the strategies sites use to implement a new practice, actions taken during the implementation process predict the achievement of program start-up and competency as measured with this tool [41, 51]. The SIC was tailored for this protocol using standardized SIC adaptation procedures [41] by the SIC developers, PrIMO model developers, and members of the research team. Consensus was reached regarding essential implementation activities for effective implementation fidelity for delivery of PrIMO, taking into consideration study start-up processes required by the Sponsor and activities that may occur through IF procedures. Study-specific milestones were mapped to the “universal” SIC to provide a low-burden observational tool to record progress of clinics over time as they implement PrIMO. Research Coordinators (RCs) at each of the sites will track and enter milestone completion dates into the web based SIC Tool.

#### Acceptability

Site staff and patient participants will complete longitudinal quantitative surveys and qualitative interviews (for a subset of participants) at various timepoints surrounding model launch (see Table 4) to assess acceptability. Site staff and patient participants will follow the same procedures for screening and enrollment: at the index (staff) or baseline (patients) visit, RCs will obtain verbal consent and conduct a brief screening to confirm study eligibility specific to the participant group (including an assessment of age, prisoner status, clinic role for site staff candidates, and length of exposure to the PrIMO model for patient candidates) before consenting potential participants. Site staff and patient participants will be compensated with $100 gift cards for each completed survey (up to six for site staff and three for patients), and $100 gift cards for the subset of participants that complete qualitative interviews (up to four for site staff and three for patients), though one site’s current union contract prohibits compensation for site staff. Staff and patient participants will self-complete quantitative survey assessments. After completing their first survey timepoint, participants will be invited to participate in qualitative interviews until participant maximums or saturation is reached. Participants will meet with research staff electronically (via Zoom) to review all significant elements of the qualitative interviews via an IRB-approved verbal consent. All study materials will be approved by the single IRB (sIRB, BRANY).

**Table 4 Tab4:** Participant assessments

		3 months pre-PrIMO launch	Launch	3 months post-launch	6 months post-launch	9 months post-launch	12 months post-launch
Site staff participants							
The applied mental health research dissemination and implementation (AMHR) measure	Participant perceptions of model adoption, acceptability, appropriateness, feasibility, reach/access, organizational climate, leadership in implementing, and general leadership skills of the clinic	✓	✓	✓	✓	✓	✓
Modified clinical sustainability assessment tool (CSAT)	Participant perceptions of the model’s clinical sustainability		✓	✓	✓	✓	✓
The medical conditions regard scale (MCRS)	Biases, emotions, and expectations of chronic medical conditions, including Type2 diabetes, depressive disorder, HIV/AIDS, alcohol use disorder, stimulant use disorder, and opioid use disorder	✓	✓	✓	✓	✓	✓
Beliefs on MOUD	Prescriber perceptions of and barriers to utilizing MOUD (specifically buprenorphine, methadone, and naltrexone)	✓	✓	✓	✓	✓	✓
Implementation citizenship behavior scale (ICBS)	Identifies critical behaviors employees exhibit exceeding their expected role to support evidence-based practice implementation		✓^b^	✓^b^	✓^b^	✓^b^	✓^b^
Change rulers	Readiness and preparedness to implement PrIMO	✓	✓	✓	✓	✓	✓
Qualitative interviews^a^	Experiences providing care for patients with OUD, including use and knowledge (or lack) of the PrIMO model	✓	✓		✓		✓
Patient participants							
		Baseline (2 weeks post-exposure)		3 months post-baseline		6 months post-baseline	
Consumer AMHR	Participant perceived acceptability of model adoption, acceptability, appropriateness, feasibility, and reach/access	✓		✓		✓	
Substance use stigma mechanism scale (SU-SMS)	Self-reported feelings of internalized stigma	✓		✓		✓	
Qualitative interviews^a^	Experiences receiving care for OUD, including knowledge of the PrIMO model and experiences within the clinic	✓		✓		✓	

^a^For a subset of enrolled participants

^b^The champion provider and pharmacist will complete this measure rating other providers, team members, and pharmacy staff

As detailed in Table 4, site staff quantitative surveys will gather demographic characteristics and assess the acceptability of the PrIMO model implementation at the sites, including local partner perceptions of model implementation via the Applied Mental Health Dissemination and Implementation (AMHR) measure [52–55] and its clinical sustainability via a modified Clinical Sustainability Assessment Tool [56], biases of treating OUD via the Medical Conditions Regard Scale [57–59], perceived MOUD stigma over time via the Beliefs on MOUD assessment [60], and change rulers of readiness and preparedness to implement PrIMO over time. Site provider and pharmacist champions will also measure implementation citizenship, the behaviors that exceed expected tasks performed by employees at the site to support the implementation of the PrIMO model, via the Implementation Citizenship Behavior Scale (ICBS) [61–64].

Patient participant quantitative surveys will gather demographic characteristics and assess the perceived acceptability of the PrIMO model via the consumer-based AMHR, and feelings of internalized stigma from the Substance Use Stigma Mechanism Scale (SU-SMS) [65] over time.

Qualitative interviews with site staff will focus on exploring all five CFIR domains through key constructs related to MOUD barriers and facilitators, knowledge about PrIMO (self-evaluation), awareness of the needs of people with OUD, staff perspectives on the PrIMO model, staff perspectives on the process of implementing the PrIMO model, and staff perspectives on the PrIMO model in the context of the work environment. Qualitative interviews with patients will focus on exploring all CFIR domains (when possible) through key constructs related to knowledge about PrIMO, PrIMO experience/encounters with care team (Fidelity check), PrIMO experience/care team networks and communications (Fidelity check), care team attitudes/stigma, PrIMO experience/education (Fidelity check), patient needs and resources, and PrIMO model characteristics.

In addition to quantitative surveys and qualitative interviews, fidelity to the model and cost will also assist in determining the acceptability of the model’s implementation. Fidelity will be measured via a checklist developed by the study team that will systematically track how various team-based aspects of the PrIMO model are implemented, including those determined to be critical to the success of the model. Sites will be encouraged to complete the checklist during weekly clinical operations meetings (which is a core component of the PrIMO model). Checklist completion will help identify areas that may require targeted IF approaches to better support adherence to the PrIMO model as well as provide insight into how clinics tailor the model for location conditions (e.g., staffing structure, workflows, etc.). The Cost of Implementing New Strategies (COINS) is a method of mapping implementation resources that will collect information on the cost of implementing the PrIMO model, using the SIC. The COINS is not a measure of cost effectiveness but rather a way to map the cost of implementation resources using the SIC. The COINS tool has demonstrated success in identifying cost and resource differences between implementation strategies in studies using the SIC [66].

#### Impact

Treatment outcomes, including a site’s capacity for MOUD, will be assessed via EHR data extracted from the clinic systems. EHR records will be extracted in coordination with a Data Dictionary developed specifically for the use of this study, which detail the fields each site will be asked to extract. At a minimum, the study will extract EHR data to explore treatment outcomes for patients on MOUD at the clinic (i.e., average retention, MOUD adherence, and toxicology including opioid abstinence), and capacity for treating patients with MOUD (i.e., the number of patients on MOUD, providers prescribing MOUD, and MOUD patients per prescribing provider) at all sites. EHR data will anchor on the launch of the model, allowing comparison of the model’s impact on these fields from 1-year pre-PrIMO launch to 1-year post-PrIMO launch at each site.

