#### Implementation Facilitation strategy

Implementation Facilitation (IF) is the comprehensive strategy incorporating a bundle of interconnected implementation activities that will be used to support and enable clinical sites to implement the PrIMO model. The IF strategy utilized in this study was manualized by Kirchner and colleagues [34] and used by study investigators in previous studies [36–39]. In this study, IF relies on a collaborative partnership between local site champions (provider and pharmacist) who have in-depth knowledge of the organization (e.g., norms, culture, change agents) and external facilitators who serve as content experts on the innovation (PrIMO model developers, addiction and psychiatry expertise, implementation researchers). Champions serve as leaders of practice change within the clinic, forging relationships with local partners, tailoring the model to site-specific conditions, and building enthusiasm. They work closely with external facilitators and serve as key liaisons between the two teams. External facilitators work with local partners and provider and pharmacist champions to conduct a formative evaluation, develop, and refine clinical procedures or resources, perform academic detailing and staff education, lead a learning collaborative offering continuing medical education units, and facilitate performance monitoring and feedback. Elements of the IF approach are outlined in Table 2.

**Table 2 Tab2:** Implementation Facilitation (IF) activities

IF activities	IF activity description
Engagement of local partners	Local partner engagement involves creating an atmosphere that is open, non-critical, and goal oriented. Engagement of key partners will take place at the administrative, provider, pharmacist, pharmacy technician, and patient levels
Formative evaluation	Formative evaluation is an implementation assessment approach designed to identify influences on the development, progress, and effectiveness of implementation efforts related to the PrIMO model and use these data to tailor, refine, and monitor the implementation of the model. Approximately two focus groups per site will be conducted with additional individual meetings with local partners. Change rulers will provide ongoing evaluation of readiness and preparedness, gathered electronically

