#### Design

This is a longitudinal mixed-methods implementation study that combines qualitative and quantitative methods using survey and EHR data. Qualitative and quantitative outcomes will be measured across sites, site staff participants (e.g., providers, pharmacists, pharmacy technicians, and administrators), and patient participants in MOUD to assess the extent of implementation and barriers and facilitators to implementation and sustainability.

Site staff must be 18 years of age or older, speak and read English fluently, employed by the participating clinic, and were exposed to the PrIMO model through an introductory email sent by the Site Principal Investigator to all staff (this email contained a letter from the model developers and a graphic explaining the six Core Components of the PrIMO model). They will be recruited via posters, emails, or word-of-mouth and after providing informed written consent will complete quantitative surveys at approximately 3 months pre-PrIMO launch, at launch, 3 months post-launch, 6 months post-launch, 9 months post-launch, and 12 months post-launch. Site staff will be invited to participate in qualitative interviews at 3 months pre-launch, at launch, 6 months post-launch, and 12 months post-launch timepoints. Site staff will have the opportunity to participate at each timepoint to best capture the model’s acceptability.

Patients must be 18 years of age or older, receiving MOUD from a provider at the participating clinic, and exposed to the model for at least 2 weeks (to best protect study data from contamination related to the clinic’s MOUD procedures prior to PrIMO launch). Patients will be recruited from the participating clinics via posters, flyers, and word-of-mouth; they complete baseline, 3-month post-baseline, and 6-month post-baseline surveys and will be invited to participate in interviews at each timepoint. Patient enrollment will last for approximately 6 months.

EHR data, including aggregate treatment outcomes from all patients on MOUD at the clinic, and administrative data, including data on provider capacity, MOUD prescribing, and staff training, will inform impact and be collected for a period of 12 months pre- and post-model launch.

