Qualitative interviews will undergo direct content analysis [67] to identify themes and subthemes found across participant subgroups. Analysis of these outcomes will be conducted at individual data collection time points (site summary matrices populated synchronously by time point) and at study completion (time-ordered, sequential site summary matrices populated diachronously).

Interviewers will use individual interview forms (i.e., ‘templated summaries’ [68]) as the analytic tools for the cross-sectional analyses, which will be populated as soon as possible following each interview. Interviewers will embed relevant text segments from interview transcripts generated by Zoom into interview forms that have been pre-coded by CFIR constructs. A secondary analyst (i.e., member of the team who did not conduct the interview) will review completed interview forms for thoroughness and accuracy. Once all interviews have been conducted at a site for a given data collection timepoint, a rapid cross-sectional analysis will be conducted for each site (site staff and patients), generating site summary matrices by timepoint (a random subset will be reviewed by secondary analysts to ensure trustworthiness)**.** Mixed method analysis, or the systematic integration of qualitative and quantitative measures of acceptability for the purposes of triangulation (seeking convergence/divergence of both types of outcome data) and expansion (seeking a more comprehensive understanding of acceptability of PrIMO and its implementation) [69, 70] will occur at study completion once all data have been collected.

The study hypothesizes that it will be feasible to implement the PrIMO model (complete SIC Stage 6) using the IF implementation approach, and that it will be acceptable, will positively impact patient outcomes one year post-model launch (e.g., increased MOUD treatment retention, medication regimen adherence, service utilization for co-morbid conditions, and decreased substance use including opioid abstinence), and will increase each clinic’s capacity for caring for patients with MOUD (e.g., increased number of patients, number of prescribers, and rate of patients per prescriber).

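### The year-before versus year-after EHR comparison has no comparator and no stated pre-launch trend, yet is worded as the model's impact

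*Protocol article*

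**What the plan says.** The Impact section under Processes and measures anchors the EHR data on launch, to allow a comparison, labelled the model's impact, that runs "from 1-year pre-PrIMO launch to 1-year post-PrIMO launch at each site". The Study population section repeats the window: "Extracted EHR data will span 1 year pre-model launch and 1-year post-model launch to explore impact at each clinic". Under Design, EHR and administrative data are to "be collected for a period of 12 months pre- and post-model launch". The measures are retention, adherence and toxicology, plus capacity: patients on MOUD, prescribers, and patients per prescriber.

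The Analysis section hypothesises that the model "will positively impact patient outcomes one year post-model launch" and will raise each clinic's capacity. The same section calls site-level analysis descriptive and the study exploratory, and says that four sites are too few for statistical conclusions.

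Under Setting, all four selected clinics implement the model. No comparison clinic, staggered launch or display of the pre-launch trend is described.

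On timing, launch is SIC Stage 6, and the Feasibility section places the start of the SIC implementation phase at Stage 4. The first staff survey comes about 3 months before launch. Change rulers, which Table 2 lists under formative evaluation as part of facilitation, accompany every staff survey. External facilitators also "perform academic detailing and staff education, lead a learning collaborative offering continuing medical education units", with no dates given. Eligible staff "were exposed to the PrIMO model through an introductory email sent by the Site Principal Investigator to all staff".

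**The concern.** Without a comparator, a contrast between the year before and the year after launch contains whatever was already changing at the site. Capacity measures are the most exposed. The Background section describes a national call to scale up MOUD delivery, which could move patient and prescriber numbers without PrIMO. The direction is not known, however: the Discussion gives a staffing shortage as a real-world problem that would affect results, and that could pull the other way.

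The 'before' year is also not clearly free of the programme. Facilitation exists to bring sites to launch, so some of it must come earlier. If it changed care early, part of the effect sits in the 'before' year and the contrast is too small. For surveyed patients, the Design section guards against carry-over from earlier clinic procedures by requiring two weeks of exposure. No similar buffer is described for the EHR comparison.

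At stake is the reading of a secondary result. A difference produced by trend could be reported as impact, and a real change could be understated, with nothing in the stated contrast to tell the two apart.

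**Working it through.** **Plan's own figure.** None. The article gives no expected impact, prior trend or power for the EHR outcomes, so the rates below are assumptions chosen to show scale.

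**Inputs from the article.** 12 months before and 12 months after launch. MOUD patients by site (Table 3): A 350, B 123, C 221, D 35. MOUD prescribers: A 5, B 4, C 48, D 7. First change rulers about 3 months before launch.

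**Step 1: trend in counts, no model effect.** Each month after launch lies exactly 12 months after its counterpart before launch. With constant growth g per month, the ratio of the two yearly averages is (1 + g)^12.

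| Assumed g per month | Ratio | Apparent change |
|---|---|---|
| 0.5% | 1.005^12 = 1.062 | +6% |
| 1% | 1.01^12 = 1.127 | +13% |
| 2% | 1.02^12 = 1.268 | +27% |
| -1% | 0.99^12 = 0.886 | -11% |

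This applies to average monthly counts.

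**Step 2: trend in percentages, no model effect.** For a measure such as adherence with a linear trend of s points per month, the difference between yearly averages is 12 × s. Assumed s of 0.25, 0.5 and 1.0 gives 3, 6 and 12 points.

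**Step 3: early effects in the 'before' year.** If k of the 12 months already carry a share f of a true effect E, the contrast shows E × (1 − f × k/12). For an assumed E of 10 points:
- k = 3, f = 0.5: 10 × (1 − 0.125) = 8.75
- k = 3, f = 1: 10 × (1 − 0.25) = 7.5
- k = 6, f = 0.5: 7.5
- k = 6, f = 1: 5.0

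The article fixes neither k nor f.

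**Step 4: both together.** With an assumed trend of 0.5 points per month, a true step of 10, and half the effect present in the last 3 months before launch, the yearly contrast is 12 × 0.5 + 10 − (3/12) × 5 = 14.75. Fitting a pre-launch slope and a step at launch to the same 24 monthly values, leaving out those 3 months, returns 10.0. With a trend of 1 point per month and no effect, the yearly contrast is 12 and the fitted step is 0. These values contain no noise, so they show only that monthly values plus the trend can separate what the yearly contrast cannot. They do not show precision at these sites.

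**Step 5: timing.** Stages 1 to 5 precede Stage 6. Unless all of that work ended more than 12 months before launch, part of it lies in the 'before' year. The change rulers, at about 3 months before launch, do lie in it.

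**The case against.** The strongest reply is that this is a feasibility study with a descriptive, exploratory secondary aim, and that an uncontrolled design was a deliberate choice. That stands, and it limits the weight of the point. It does not remove the wording in the Impact and Analysis sections, which attributes the difference to the model.

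A second reply is that the 12 months on each side define a data window, and that a fuller protocol or SAP may cut the data by month. This is fair. A reader might infer that each year will be collapsed to one value; that is the natural reading, but the article does not say so. The point therefore rests on the stated contrast and its wording, not on missing detail.

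Three further readings go beyond the documents:
- **A quarter of the 'before' year is contaminated.** The 3 months run from an introductory email holding a letter and a graphic, which Table 2 does not list as facilitation. They are not months of altered care.
- **The 'before' year contains the main facilitation activities.** Academic detailing and the learning collaborative are undated.
- **The bias is upward.** No site's prior trend is given, so its sign is unknown.

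It can also be objected that segmented regression fits poorly here: three sites have 4 to 7 MOUD prescribers, Site D has 35 MOUD patients, and implementation continues after launch rather than stepping at once. That stands, and the model should be optional.

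**Conclusion.** The concern holds in limited form. The stated EHR contrast cannot distinguish the model's effect from an existing trend, and some preparation falls inside the 'before' year, yet the result is worded as impact. Under the assumed growth of 0.5% to 2% per month in MOUD patients, trend alone gives a 6% to 27% rise. A falling trend would hide a benefit, and early effects of preparation would shrink the contrast. The actual trend, the start of facilitation and its effect on EHR outcomes are not in the article, so neither the net direction nor the size of the bias can be stated. The primary outcome is untouched. This is a correction of display and wording that should be made, not a flaw in the design.

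**What to change.** 1. Show the capacity and treatment measures at each site by month, or by quarter where counts are small, with the pre-launch trend drawn. Show retention by cohort of treatment start, because it is a duration and does not fit calendar months.
2. Use the dates recorded in the SIC tool and the activity logs to mark the span from first facilitation activity to launch as a transition period. Add a sensitivity summary that leaves it out.
3. In the Impact and Analysis sections, describe the result as change after launch relative to the pre-launch trend at these four sites, in place of the model's impact.
4. Optional: segmented regression, only where counts support it, and a longer retrospective extraction so that more months precede the first facilitation activity.

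The cost of items 1 to 3 is a little more tabulation. Because the Design section describes aggregate treatment outcomes, check that the extraction carries dates fine enough for monthly or quarterly cuts. Trends will be imprecise at Site D and for prescriber counts at Sites A, B and D, and the report should say so. Item 4 would add extraction work at the sites.
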